### Secondary outcome measures

Bipolar medication adherence will also be collected using the TRQ for medication targeting mood symptoms including lithium, anticonvulsants, antipsychotics, and antidepressants [58]. Psychiatric symptoms will be assessed using the Brief Psychiatric Rating Scale (BPRS) [59], a clinician rated measure that evaluates the spectrum of symptoms seen in individuals with BD including mania, psychosis, depression, and disorganization. The Montgomery-Asberg Depression Rating Scales (MADRS) [60], a well-validated clinician rated measure, will also be used to measure symptoms of depression and suicidality.

Researchers will utilize self-report questionnaires comprised of the Medication Adherence Self-Efficacy Scale (MASES-R) [61], the Self-Report Habit Index (SRHI) [62], the Beliefs about Medicines Questionnaire (BMQ) [63], and the Attitudes toward Mood Stabilizers Questionnaire (AMSQ) [64] to capture possible moderators and mediators to medication adherence. Dose of intervention (frequency of texts) and engagement (% texts answered) will be collected from the iTAB-CV system. Intervention acceptability/satisfaction will be assessed via questionnaire as well as open-ended process measures regarding ease of use of the system and how it can be improved. Healthcare utilization will also be measured via self-report questionnaire.

## Data collection and management

Study data will be collected and managed using REDCap, a secure, web-based application designed to support data capture for research studies providing (1) an intuitive interface for validated data entry, (2) audit trails for tracking data manipulation and export procedures, (3) automated export procedures for seamless data downloads to common statistical packages, and (4) procedures for importing data from external sources [65]. Only study team members will be able to access the REDCap project which saves to HIPAA protected servers. Data files, including analysis files, will be password protected to permit access and modification only by authorized persons. Participant names or similar potential identifiers (e.g., addresses, hospital record numbers) will not appear in any computerized database.

Lists of potential participants will be saved within the secure server and will only be accessible by study staff who have been research credentialed. For those participants who cannot be contacted, refuse participation, or otherwise do not qualify for the study, only aggregate numbers will be retained to keep track of recruitment efforts. Careful attention will be given to confidentiality, which will be maintained using subject identification (ID) codes for enrolled participants. The list that links study ID codes with subject names and all forms bearing subject names and contact information will be stored in password protected files on the institution’s secure server. Research files are not and will not be available to any unauthorized person.

Rigorous development of data collection forms, training of staff on the proper completion, and checking of data collection forms will reduce errors at the point of collection. Additional data management practices before and after entry into the database will identify potential problems or outlying values and will catch other errors on data collection forms. Data management staff will be responsible for tracking forms entered and for performing routine auditing data checks. Analytic data sets will be prepared using STATA v13.1 [66].

### Data analysis plan

For the primary intent-to-treat analyses (aims 1 and 2), linear mixed effects longitudinal analysis of adherence (TRQ past month is primary) and SBP to 4 months (V2) will be conducted. A treatment variable will be included to indicate randomization to either iTAB-CV + SM or SM alone. Secondarily, we will also consider models with longer-term outcomes. Within the longitudinal models, significant interaction of the treatment variable with time indicates that the treatments have a different course of response. The researchers will first fit models with time as a covariate and, alternatively, consider time period as a categorical variable. Time by treatment interaction will be of primary inferential interest. To account for possible imbalances across treatment groups and other sources of variation, explanatory variables such as gender, ethnicity, and BD diagnosis type (I vs. II) will be considered for inclusion in the mixed models.

Researchers will consider representing TRQ scores as binary outcomes, indicating whether or not an adherence threshold has been met (e.g., 80% adherent). Researchers will thus also consider generalized linear mixed models for binary outcomes (SAS PROC GLIMMIX), as well as fitting a longitudinal model on the difference values with baseline value adjustment. Graphical methods will be used extensively to examine distributions of residuals, identify potentially influential points, and guide data transformations to better approximate normality if warranted. Sensitivity analysis of results will be conducted by modeling a range of plausible correlation structures.

In secondary analyses for both aims 1 and 2, follow-up at 6 and 12 months (V4 to V6) will also be compared in the respective longitudinal analyses for adherence and SBP. The researchers will conduct contrast analyses of treatment by (discrete) time interaction at time periods V4 and V6 and differences from baseline in treatment dose-level subgroups (higher versus lower booster levels) at V4 and V6 using two sample *t*-tests or nonparametric Mann-Whitney tests. Additionally, the researchers will compare corresponding TRQ and eCAP™ adherence levels. Correlation between the measures will be estimated and Bland-Altman plots will be generated [67].

The researchers will model secondary outcomes over time in a similar manner as in aims 1–2 through longitudinal mixed models when appropriate. The researchers will consider generalized linear models when distributions of outcomes are not approximately normally distributed or transformations of outcome variables to normality. The researchers will also conduct exploratory moderator analyses of the explanatory variables in the primary mixed models for adherence and SBP. Moderators to be explored include depression, psychiatric symptoms, age, sex, engagement, medication attitudes, self-efficacy, and BD type I vs. II for each of the primary outcome models. For moderator analyses, in an exploratory manner, the researchers will consider the addition of interaction effects with treatment and time for each potential moderator.

For aim 3, habit strength scores will be analyzed as an outcome in a similar manner as in aim 1. The researchers will assess dose (frequency of texts), depression, engagement, medication attitudes, and self-efficacy as moderators of habit strength. The researchers will also consider habit strength as a mediator for improved longer-term adherence at 4, 6, and 12 months. The researchers will conduct mediation analyses using approaches described by MacKinnon [68] and Preacher and Hayes [69]. These analyses will involve the treatment variable and change in adherence values. Bootstrapping methods will be used to assess indirect effects, as in Preacher and Hayes [69]. The research team will also consider, as needed, use of generalized linear models through a mediation formula approach [70, 71] to estimate the direct effect of the treatment and indirect effects through the proposed mediator.

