**Fig. 1 Fig1:**
[figure not shown]
Two-stage RCT design

In stage 2, following the month 4 assessment, those in iTAB-CV + SM will be re-randomized to receive either a high intensity (starts off with 1 reminder per day and tapers down to 1 reminder per week over the course of 2 months) or low intensity (1 reminder per week) booster. Adherence will be assessed by phone at month 5 as an interim measurement and an in-person assessment will occur at month 6. In stage 3, participants will be followed for another 6 months without intervention with one interim phone assessment and a final in-person assessment at month 12.

As this is a group of participants who may be particularly difficult to engage and retain in longitudinal research studies, there will be a number of measures taken to optimize retention. These include scheduling visits at maximally convenient times for participants, conducting visits remotely when possible, allowing for frequent breaks as needed during the procedures, hiring and training staff that will be flexible and attentive to the individual’s needs, and frequent opportunities for questions and feedback. Participants will also receive small items with the study logo of nominal monetary value but that will remind them of study participation such as a stress ball in the shape of a heart, pen to log adherence, and hand-sanitizer. Reminder calls will be made prior to assessments. Should there be challenges in meeting enrollment goals, the study team will request input from the SAB in additional procedures and processes that might optimize enrollment. Participants in all treatment groups will be compensated for assessments.

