### Randomization

The study biostatistician will generate the allocation sequence and randomization lists will be computer-generated and integrated into a REDCap randomization project. Members of the study staff will not have access to the sequence prior to assignment. Stratified randomization will be employed to ensure that equal numbers of iTAB-CV + SM and SM patients are balanced with respect to sex and BD severity as reflected by BD type (type 1 vs type 2). The second randomization (high or low booster) will also be balanced with respect to sex and BD type. The MIs will randomize participants to an intervention at baseline using the REDCap project with pre-populated randomization criteria. The MIs will also conduct the second randomization of the iTAB-CV + SM group to booster, which is set up in the iTAB-CV texting system. RAs who complete assessments will be blind to condition by not having access to the randomization module or iTAB-CV system and administering assessments relevant to both arms regardless of assignment. Only the MIs are aware of randomization assignment and they do not carry out any assessments. While all efforts will be made to keep RAs blind to treatment condition, participants are not blinded to condition and thus could unintentionally reveal information to the RAs during an assessment or outreach by an RA in response to extreme moods. Given that this is not a drug trial and risk is low for both groups, there are no plans for intentional unblinding.

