### Assessments and outcomes

Assessments for both iTAB-CV + SM and SM alone will include evaluation of medication treatment adherence, psychiatric symptoms, health status, self-efficacy for medication taking behavior, illness beliefs, medication attitudes, and habit strength for medication taking behavior. One-on-one assessments will be conducted at 5 time points over a 12-month time period. Adherence and BP will be measured at each of the 5 one-on-one assessments. There will be 3 additional remote/phone assessments which will collect adherence and BP data only. Individuals who drop out of the intervention, and who agree, will be followed up with outcomes assessments over the same 12-month time period that they would have been evaluated had they remained in the study.

Table 2 shows the variable constructs, how they will be measured, mode of data collection, and time points, following the structure of a SPIRIT figure. Demographic and clinical variables measured at baseline will include age, sex, race/ethnicity, education, marital status, and health status. Assessment visits include one-on-one screening, baseline (2 months), V1 (3 months; by phone), V2 (4 months), V3 (5 months; by phone), V4 (6 months), V5 (9 months; by phone), and V6 (12 months). All assessments will be done by a RA trained by the PIs with pre-established and documented reliability standards. Training will use video clips of non-study volunteers or actors. It is expected that patient assessment will require approximately 90 min for the screening assessment and approximately 60 min for the follow-up assessments. Study visits designated as one-on-one may take place in person, via phone or via video conferencing as needed.

**Table 2 Tab2:** Study instruments and assessments schedule

Construct	Measurement	Mode	Screen	BL	V1 phone	V2	V3 phone	V4	V5 phone	V6

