From the pilot data, mean screen SBP was 144.81 (SD 15.46). Change from screen to 3 months with the iTAB-CV intervention saw a mean reduction in SBP of 8.78. Reductions in BP of at least 2 mmHg can significantly reduce the incidence of cardiovascular disease and its complications in both hypertensive and normotensive individuals, and reductions of the magnitude seen in this team’s pilot work is well above thresholds that are considered clinically meaningful [75]. Based on our preliminary mixed model, the researchers also observed compound symmetry correlation parameter value of 0.36. This covariance model had similar model fit as with an AR(1) model in terms of AIC/BIC criteria and parameter estimate values. The researchers will assume no SBP pressure change is observed in the SM arm and estimated error standard deviation of 15.46, as observed [38]. Finally, in a linear mixed model with participant-level random effects, with two-sided type I error of 0.025, power = 0.80 for the projected sample size of 182 participants. The study staff will target a sample of 200 for the study to allow for some deviation from assumptions. Thus, the researchers should have sufficient statistical power for the first 2 primary aims.

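### The high-versus-low booster comparison uses unadjusted change from the month 2 baseline and leaves out the month 4 value and the balancing factors: unbiased, but with about 1.5 (SBP) to 2 (TRQ) times the variance of an adjusted analysis

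*Protocol article*

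**What the plan says.** In the Data analysis plan, the secondary analyses for aims 1 and 2 compare "differences from baseline in treatment dose-level subgroups (higher versus lower booster levels) at V4 and V6". The named methods are the two-sample t-test or, as the nonparametric alternative, the Mann-Whitney test. Neither takes a covariate.

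The study baseline is month 2 (Assessments and outcomes). The booster is assigned later. The text after Fig. 1 states: "In stage 2, following the month 4 assessment, those in iTAB-CV + SM will be re-randomized". The value measured just before that assignment exists for both outcomes, since "Adherence and BP will be measured at each of the 5 one-on-one assessments" and V2 is one of those visits. The Randomization section adds: "The second randomization (high or low booster) will also be balanced with respect to sex and BD type".

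Baseline adjustment and explanatory covariates are mentioned in the Data analysis plan only for the longitudinal models. The later paragraph headed by aim 3 deals with habit strength and gives no other high-versus-low comparison of SBP or adherence.

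**The concern.** Booster intensity is one of the four stated aims and the reason for the second randomisation. Only the iTAB-CV arm of 100 is re-randomised, so an even split gives about 50 per level, or 37.5 after the assumed 25% attrition. Precision is scarce at that size. The planned test takes a difference from an earlier value that is only weakly correlated with the outcome. It leaves out the V2 measurement, taken immediately before the booster is assigned, and the two factors on which that assignment is balanced. What is at stake is how small a booster difference the trial can detect, using data it will collect anyway.

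**Working it through.** **Inputs from Sample size calculations.** SBP: SD 15.46 and "compound symmetry correlation parameter value of 0.36". TRQ: AR(1) correlation 0.44 and error variance 308 (SD √308 = 17.55). Attrition 25%; 100 per arm. I treat the SD as the total SD at one visit; the variance ratios do not depend on it.

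**Reproducing the plan's own figure.** The protocol gives no power or variance for the booster comparison. The nearest figure with the same SBP inputs is the total of 182 for the primary SBP analysis. For a linear group-by-time contrast, n per arm = 2(z₀.₉₈₇₅ + z₀.₈₀)² · c′Σc / (c′d)². Taking four equally spaced times (my assumption; the article does not give the number), c = (−3, −1, 1, 3):
- c′Σc = 15.46² × (1 − 0.36) × 20 = 3059
- c′d = 8.78 × 10/3 = 29.27
- n = 2 × 9.505 × 3059 / 29.27² = 67.9, so 68
- 68/0.75 gives 91 per arm, 182 in total.

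The figure is matched, so the SBP inputs are being read as the protocol intends. With two or three times the total is 202 to 204.

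**Variance of the booster contrast, per unit σ².** Let r be the correlation between the outcome and the earlier value used.
- Unadjusted change from an earlier value: 2(1 − r)
- Raw outcome, no adjustment: 1
- Outcome adjusted for one earlier value: 1 − r²
- Adjusted for baseline and V2 under compound symmetry: 1 − 2r²/(1 + r)

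| Analysis | SBP (V4 and V6) | TRQ at V4 |
|---|---|---|
| Change from baseline (planned) | 2(1 − 0.36) = 1.28 | 2(1 − 0.44⁴) = 2(1 − 0.0375) = 1.925 |
| Change from V2, unadjusted | 1.28 | 2(1 − 0.44²) = 2(1 − 0.1936) = 1.613 |
| Raw value | 1.00 | 1.00 |
| V2 as covariate | 1 − 0.36² = 0.870 | 1 − 0.1936² = 0.963 |
| Baseline and V2 as covariates | 0.809 | 0.963 |

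The TRQ column applies 0.44 per month, which is the same as per scheduled visit between baseline and V4.

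**Ratios of the planned analysis to V2 adjustment.** SBP: 1.28/0.870 = 1.47 (1.28/0.809 = 1.58 with both covariates). TRQ at V4: 1.925/0.963 = 2.00. At V6 the TRQ ratio is also about 2.0, or 1.90 if 0.44 applies per in-person visit.

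**Where the loss comes from.** Unadjusted change from V2 has the same SBP variance as change from baseline (ratio 1.00). For TRQ the ratio is 1.925/1.613 = 1.19. The starting point therefore explains little. Below a correlation of 0.5, subtracting an earlier value is worse than using the raw outcome, and that accounts for most of the loss.

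**Detectable difference** = (1.960 + 0.842) × SD × √(2 × factor / n), for 80% power and two-sided 0.05 (my assumption; no level is given for this comparison).

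| n per group | SBP planned | SBP, V2 covariate | TRQ planned | TRQ, V2 covariate |
|---|---|---|---|---|
| 37.5 | 11.3 mmHg | 9.3 (9.0 with baseline too) | 15.8 points | 11.1 |
| 50 | 9.8 mmHg | 8.1 | 13.6 points | 9.6 |

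**Sensitivity to the correlation.** Under compound symmetry at 0.5, 0.6 and 0.7, the ratio to V2 adjustment is 1.33, 1.25 and 1.18. With baseline also a covariate it is 1.50, 1.45 and 1.42.

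These figures are for the t-test. No figure was computed for the Mann-Whitney test, which is applied to the same unadjusted differences.

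**The case against.** Two stronger readings are tempting, and neither is supported. The first is that measuring change from month 2, when the booster starts at month 4, itself causes the inflation. The table shows otherwise: moving the subtraction to V2 gains nothing for SBP and a factor of 1.19 for TRQ. The second is that a chance V2 difference between booster groups would be read as a booster effect. The booster is randomised, so the planned contrast is unbiased and chance imbalance is already covered by the test's error rate. Under the stated structures the covariance of V4 minus baseline with V2 is also zero: 0.36 − 0.36 for SBP and 0.1936 − 0.1936 for TRQ.

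Other points on the plan's side have weight:
- Objectives words aim 3 as high and low booster against SM alone at 6 months. SM participants are not re-randomised, so the month 2 baseline is the reference common to all three groups. This justifies that baseline for comparisons with SM. It does not cover the t-test, which is a high-versus-low contrast within the re-randomised arm.
- The comparison is exploratory. At 37.5 per group even the adjusted SBP figure of 9.3 mmHg exceeds 8.78 mmHg, the whole projected iTAB-CV effect. Adjustment improves the comparison without making it well powered.
- The size rests on pilot correlations, and 25% attrition comes from a 12-month trial. The gain shrinks at higher correlations but stays above 1.
- An unadjusted test after stratified randomisation is valid, and an article may leave covariate detail to the SAP. Here, however, the article names both the response variable and the test.

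**Conclusion.** The point holds as a loss of precision, not as bias. As written, the high-versus-low comparison has about 1.47 times (SBP) and 2.0 times (TRQ at V4) the variance of an analysis with the V2 value as covariate. In effect, 100 re-randomised participants would give the precision of about 100/1.47 = 68 for SBP and 50 for TRQ. This assumes that the pilot correlations and covariance structures carry over to the trial and that the booster split is even. The absolute detectable differences also depend on the assumed two-sided 0.05, 80% power and group sizes. The finding is confined to a secondary, exploratory comparison.

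**What to change.** For the high-versus-low contrast, replace the t-test or Mann-Whitney test on change from baseline with ANCOVA or a mixed model in the re-randomised participants. Use the outcome at V4 and V6 as response, with the V2 value, the month 2 baseline value, sex and BD type as covariates, and estimate the booster effect separately at each visit. Do not simply redefine the change score as change from V2.

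Keep the comparisons of each booster group with SM alone in the longitudinal model referenced to the month 2 baseline. Do not adjust those for V2, which is a post-randomisation value for that comparison.

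The cost is a change of wording in the analysis plan, ideally made before outcomes are looked at by booster level. No extra visits, measurements or participants are needed.

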iTAB-CV is personalized with texts that are specific to the person, medication, and timing. Motivational interviewing demonstrates that change is more effective when patients use their own words to commit [45] and personalization of messages has been effective in changing behaviors in other diseases such as HIV-infected individuals with BD and in diabetes [46–48]. Moreover, iTAB-CV uses the participant’s own words for both reminders and reinforcers. Personalizing reminders and reinforcers offer an advantage over previous studies that have focused on medication timing and dosing but did not tailor the reminder itself [46–49]. Participants will be encouraged to write their own adherence reminders (e.g., I want to stay healthy so I can care for Sam and Jane for many years!”) as well as reinforcement stems within the character limits (e.g., “Susie is so proud of you for taking your meds!”). Participants will choose their preferred name for HTN and BD to be used in some of the text stems and will have the opportunity to opt out of 2 of 12 categories: Social Support and Spirituality. In those cases, Social Comparison texts, customized texts, and alternate texts will be substituted.

Adherence texts will be followed by a question asking whether medication was taken. All responses will be followed by immediate reinforcement either to reinforce medication taking behavior or to reinforce engagement with the system if response indicates medicine was not taken (see Fig. 2 for sample text and reinforcement exchange).

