**Primary outcomes**										
Blood pressure	Systolic blood pressure	REDCap	X	X	X	X	X	X	X	X
Antihypertensive adherence	TRQ	REDCap	X	X	X	X	X	X	X	X
	eCAP™			X	X	X	X	X	X	X

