Antihypertensive medication adherence will be evaluated with the self-reported Tablets Routine Questionnaire (TRQ) [52, 53] for the past week and the past month. Self-reported adherence will be validated with the eCAP™. While the literature on measurement of adherence including the co-PIs’ own work in this area acknowledges limitations for all methods of adherence assessment, both self-report and automated pill-caps appear valid and practical for use in BD studies [21, 54].

At screening, participants will be asked about their demographic information and current medication taking behaviors to determine if they meet inclusion criteria. Participants will also undergo a diagnostic interview based on the DSM and ICD psychiatric disorders called the Mini-International Neuropsychiatric Interview (MINI) [55] to confirm BD diagnosis and assess for suicidality. Data on comorbid medical conditions will be collected based on the self-report version of the Charlson Comorbidity Index (CCI) [56]. While the original CCI includes dementia, it was excluded from the self-report version given that those with dementia would not be able to provide informed consent. Finally, participants will be administered the Rapid Estimate of Adult Literacy in Medicine-Revised (REALM-R) [57] to assess health literacy.

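### The primary adherence result is unblinded self-report, and the stated eCAP analyses do not address over-reporting that differs by arm

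*Protocol article*

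**What the plan says.** **Primary measure.** The Data analysis plan states: "linear mixed effects longitudinal analysis of adherence (TRQ past month is primary) and SBP to 4 months (V2) will be conducted". The section Assessments and outcomes describes TRQ as self-report.

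**Blinding.** Under Randomization, assessors are kept blind, but "participants are not blinded to condition".

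**What only one arm receives.** Under Intervention: "Adherence texts will be followed by a question asking whether medication was taken". Every reply is reinforced: a yes for the behaviour, a no for engaging with the system. Texts are daily for the two months after baseline, which is the primary analysis period. The self-monitoring arm receives mood-rating and refill texts only.

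**Role of eCAP.** All participants use the device. Table 2 places it from baseline to V6 under the primary construct "Antihypertensive adherence", beside TRQ. Assessments and outcomes gives its purpose: "Self-reported adherence will be validated with the eCAP™". The Data analysis plan gives its use: "Additionally, the researchers will compare corresponding TRQ and eCAP™ adherence levels", followed by a correlation and Bland-Altman plots. Neither arm nor visit is mentioned there. The secondary outcomes sent to mixed models do not, in Table 2, include eCAP. The named sensitivity analyses concern correlation structure and missing data, not measurement error.

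**The concern.** Blinded assessors do not protect an outcome that the participant reports. During the primary period one arm repeatedly answers a question about the behaviour that TRQ measures, and the other does not. This is a plausible reason for reporting to shift more in one arm.

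A randomised comparison removes reporting error that is equal in both arms, but not error that differs. Agreement between TRQ and eCAP, described without regard to arm, says how closely the measures track each other overall. It does not say whether the TRQ arm difference is pill-taking or reporting. At stake is an adherence benefit claimed on its own 0.025 when the device in the same trial might not show one.

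**Working it through.** **Inputs (Sample size calculations).** Error variance 308 (SD 17.55); AR(1) correlation 0.44; two-sided alpha 0.025 (critical value 2.241); power 0.80 (0.842); projected difference 16.1 points; 100 per arm; 25% attrition. I take 308 as the variance at one visit and 0.44 as the correlation between adjacent visits. Visits in the primary period are BL, V1 and V2.

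**The protocol's own figure.** Total N = 4 × (2.241 + 0.842)² × Var(change) / 16.1².
- Two visits: Var = 2 × 308 × (1 − 0.44) = 345.0, so N = 50.6, or 67.5 after dividing by 0.75.
- Three visits: Var = 2 × 308 × (1 − 0.44²) = 496.7, so N = 72.9, or 97.1 after dividing by 0.75.

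The stated figure of about 78 lies within this range. The number of visits and the attrition pattern are not given, so it cannot be reproduced uniquely. Nothing below depends on it.

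**Standard error of the arm difference in BL-to-V2 change.** With complete data, SE = √(Var(change) × 2/n per arm). With dropout, it comes from the generalised least squares information summed over dropout patterns.

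**Effect of reporting bias.** Let b be the extra over-reporting in iTAB-CV at V2 (growing linearly from baseline if time is linear), with no true effect. The probability of significance is essentially Φ(b/SE − 2.241). The values of b are assumptions; the document gives none.

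| Case | SE | Smallest significant difference | b = 5 | b = 8 | b = 10 |
|---|---|---|---|---|---|
| Two visits, 100 per arm, no dropout | 2.63 | 5.9 | 0.37 | 0.79 | 0.94 |
| Two visits, 75 per arm | 3.03 | 6.8 | 0.28 | 0.65 | 0.85 |
| Three visits, no dropout | 3.15 | 7.1 | 0.26 | 0.62 | 0.82 |
| Three visits, attrition rising linearly to 25% at V2 | 3.42 | 7.7 | 0.22 | 0.54 | 0.75 |
| Three visits, only 75 per arm throughout (outer case) | 3.64 | 8.2 | 0.19 | 0.48 | 0.69 |

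The fourth row matches the planned visits best and is the main case; linear and categorical time give nearly the same SE (3.42 and 3.43). It is cautious, because the 25% comes from a 12-month trial and V2 is at month 4. In every row, the smallest significant difference is about half the projected 16.1 points or less.

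**What agreement without regard to arm would show.** With equal arms, a bias b in one arm moves the overall mean of TRQ minus eCAP by b/2 and adds b²/4 to its variance. For b = 8 the shift is 4 points. If the within-arm SD of the difference is assumed to be 17.55, the overall SD becomes √(308 + 16) = 18.0. Such a plot looks much like one with a 4-point bias shared by both arms, which would do no harm.

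**Could eCAP support a between-arm analysis?** No eCAP SD is given. Differences detectable at 80% power with 75 per arm:

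| Assumed eCAP SD | BL–V2 correlation 0.44 | BL–V2 correlation 0.44² |
|---|---|---|
| 17.55 | 9.4 | 11.2 |
| 25 | 13.3 | 16.0 |
| 30 | 16.0 | 19.2 |

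Except in the least favourable cell, an effect of 16.1 points would be detectable without a larger sample.

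**The case against.** **The text leaves room for more.** Naming past-month TRQ as primary implies that other adherence measures may be modelled, and Table 2 lists eCAP under the same outcome. The article does not say that agreement will be assessed with the arms combined. A reader might infer that a between-arm eCAP analysis is ruled out, or that differential reporting would necessarily pass unnoticed. The document supports neither; by-arm plots are compatible with it. What stands is narrower: the article fixes the primary measure and describes the validation, and that description contains no step that separates the arms.

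**The mechanism is plausible, not demonstrated.** Replies that medicine was not taken are reinforced too, so the texts do not simply reward a yes. TRQ is collected separately by blinded assessors. Both arms know that a device records openings, which may restrain over-reporting. These points lower the likely size of b; they do not show it to be zero.

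**SBP is co-primary and device-measured.** A gain in reporting alone should not lower blood pressure. This corroboration is indirect: SBP is a separate hypothesis with its own 0.025, and adherence can be claimed without it.

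**Self-report as primary is a declared choice.** The protocol regards both methods as valid and practical. eCAP records openings of a bottle holding one medicine, so it cannot simply replace TRQ. This stands, and the recommendation respects it.

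**Conclusion.** The point holds as a weakness in the stated analysis, not as proof of bias. As written, the eCAP validation does not address over-reporting that differs by arm, although the data to do so are collected in both arms from baseline. In the main case, with no true effect, an assumed differential over-reporting of 5, 8 or 10 points gives a significant TRQ result with probability 0.22, 0.54 or 0.75, against a nominal 0.025. With the smallest SE examined, the figures are 0.37, 0.79 and 0.94.

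These figures rest on the protocol's variance and correlation and on bias sizes that I assumed. They show sensitivity to such a bias, not how likely it is.

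A reader might also infer that the adherence claim should be barred unless the eCAP estimate points the same way. That does not follow: with no eCAP effect, chance alone would meet such a rule about half the time.

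**What to change.** Keep past-month TRQ as primary, and amend the Data analysis plan as follows before any data are seen by arm:

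1. Name the same treatment-by-time mixed model, fitted to past-month eCAP adherence at BL, V1 and V2, as the key supportive analysis, reported beside the TRQ result. The second run-in month already provides the baseline value.
2. Do the TRQ–eCAP agreement by arm and by visit. Give an estimate and confidence interval for the arm difference in TRQ minus eCAP, limited to the medicine in the eCAP bottle where TRQ is available for that medicine.
3. State that an adherence benefit will be interpreted in light of both results, without a formal directional rule.

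This needs no new visits, devices or participants, only a little more analysis. The downside is that eCAP covers one medicine and may miss doses or uploads, so the two measures may disagree for reasons other than reporting. The plan should say so in advance.
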